Secondary outcomes include mental health and quality of life assessments at 30 and 180 days after hospital discharge, assessed via telephone follow-up after obtaining verbal informed consent. Questions will be asked in reference to the index hospitalization. PTSD symptoms will be measured using the PTSD Checklist for DSM-5 (PCL-5), a validated 20-item (score 0–4, Likert scale) self-reported measure that assesses 20 DSM-5 symptoms of PTSD (clinically significant symptoms = PCL-5 > 32) [61]. While PTSD is our main secondary outcome of concern, depression, anxiety, and impaired quality of life (QOL): (1) often co-exist with PTSD; (2) are common after critical illness; and (3) are also sequela linked to AWP [1, 2, 5, 7, 10, 25, 62, 63]. To give a broad picture of burden endured by survivors, we will assess for depression and anxiety with the Hospital Anxiety and Depression Scale (HADS), a validated 14-item (7 depression, 7 anxiety, ordinal score 0–3) questionnaire commonly used in critical illness [25]. We will evaluate QOL with EuroQol-5D (EQ-5D), the most widely used scale for measuring health-related QOL and part of the core sets recommended for critical care studies on post-discharge outcomes [64, 65].

To assess for potentially modifiable intervention targets for future trials aimed at PTSD symptom prevention, we will collect patient perception of (1) perceived threat; (2) clinician compassion; and (3) degree of family/friend emotional support. Perceived threat will be measured with the validated 7-item tool used in our prior work [19, 38, 66, 67]. Patient perception of clinician compassion will be assessed with a 5-item measure, developed, and validated by our team (only instrument validated for ED use) [68]. Family/friend emotional support during hospitalization will be assessed with two items previously used in the ED as measures of anxiety-provoking social support that are significantly associated with PTSD symptoms: (1) “How much of the time did your support person need you to comfort them?”; and (2) “How much of the time did your support person make you anxious?” [69].

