Instrumental variable (IV) methods will be used to account for non-adherence, as there could be differences between intervention effectiveness (i.e., effect among all patients to whom the intervention is targeted) and efficacy (i.e., effects among patients whose clinicians adhere to the intervention). We will use a non-parametric IV estimator adapted to stepped wedge designs, and IV regression methods to estimate complier average causal effect (CACE) of the intervention [79]. To avoid conflating the effect of time with the intervention effect, we will (1) obtain step-specific CACE estimates and (2) summarize step-specific estimates across all steps. We will also use two-stage residual inclusion to perform IV regression, using individual data from all six time points, adjusting for time and cluster effects [80–82]. Unlike per-protocol analyses, CACE analyses are not biased by selection effects and have been shown to be valid inferential approaches in stepped wedge trials [79].

We will determine proportion (with 95% CIs) of patients with clinically significant PTSD symptoms (PCL-5 score > 32) at 30 days and 180 days post-discharge [83, 84] and compare the control versus the intervention phase. To test the independent association of AWP (main exposure of interest) with 30-day PTSD symptom development, multivariable logistic regression will be used, with covariates selected for inclusion a priori [85]. The model will be adjusted for covariates previously associated with PTSD symptoms in critical illness survivors: (1) age; (2) sex; (3) prior psychological trauma (PC-PTSD-5 score)/mental health history; (4) illness severity; and (5) receipt and dose of benzodiazepines [10, 25, 26, 62, 86, 87]. We will adjust for race, given known racial disparities in PTSD symptoms [88–91]. To examine time trends in PTSD symptoms, and independent effects of AWP on time trends, mixed effect logistic regression will be used. Individual random intercept and random time slope will be specified and tested along with other potential risk factors. We will identify individual-level potential risk factors which could explain variation in individual time trend by testing interaction between random time slope and risk factor(s). In all of these models, cluster effect will be modeled as a fixed effect, using cluster indicator in the model. Similar analyses will be conducted for the other secondary outcomes.

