### Sample size justification

Our sample size is designed to detect a difference in the proportion of patients experiencing AWP in the control versus the intervention phase. The sample size must be inflated by estimating the design effect, to account for the intraclass correlation coefficient (ICC). More common outcomes are associated with higher design effects, whereas lower prevalence outcomes, such as AWP, have smaller ICCs [94]. Based on our data, and extensive supporting analyses from more than 100 ICC values obtained from research studies and population health outcomes analyses (*n* > 1,000,000 patients) which show a strong linear association between the ICC and outcome prevalence in clustered binary data, we conservatively estimate an ICC of 0.001 [94]. From our preliminary multicenter data, due to a reduction in rocuronium use, it is reasonable to estimate a reduction in the proportion of patients experiencing AWP from 4.0% in the control phase to 0.2% in the intervention phase (data from the operating room), which would require a total sample size of 1650 patients [95]. To err on the side of conservative assumptions, and to account for possible non-adherence during the study, we will assume a prevalence of AWP of 3.3% in the control phase and 0.6% in the intervention phase. These conservative estimates are based on our prior work (control phase), and the intervention phase event rate is similar to that seen in operating room patients managed with total intravenous anesthesia and when longer-acting NMB is limited [10, 19, 96]. Thus, these calculations are both clinically important (would prevent ~ 10,000 AWP cases annually in the USA) and plausible from supporting preliminary work. Considering there are 5 sites and 6 time periods, for 80% power with *α* of 0.05, we will need a total sample size 3090 patients.

With respect to PTSD, if we estimate that PTSD occurs in 45% of those with AWP [5, 6, 9] and 20% of the rest of the cohort [25–27], assuming *α* = 0.05 and power = 0.80, using two-sided *Z*-test with pooled variance, a sample size of 1192 patients will be required for the multivariable model above. With respect to perceived threat, even if correlation between perceived threat and PTSD symptoms is smaller than our prior work (0.3) then a minimum of 412 patients is estimated to detect the mediated effect of perceived threat between clinician compassion and PTSD symptoms [38, 97, 98].

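### The PTSD time-trend model puts a random time slope on a binary outcome measured twice; the slope variance cannot be learned from those data, and the time effect depends on it

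*Protocol article*

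**What the plan says.** Under Outcome measures, the protocol article sets the schedule: "Secondary outcomes include mental health and quality of life assessments at 30 and 180 days after hospital discharge". Table 1 agrees, marking the mental health and quality of life assessments at day 30 and day 180 and nowhere else. The PTSD outcome is dichotomised: "clinically significant symptoms = PCL-5 > 32". The PC-PTSD-5 named in the analysis section is a covariate for earlier trauma, not a third PCL-5 measurement.

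Under Proposed statistical methods, the longitudinal model is fixed: "To examine time trends in PTSD symptoms, and independent effects of AWP on time trends, mixed effect logistic regression will be used". Its random part is fixed too: "Individual random intercept and random time slope will be specified and tested along with other potential risk factors". The plan then looks for patient-level factors that might "explain variation in individual time trend by testing interaction between random time slope and risk factor(s". Cluster enters as a fixed effect. The approach is carried further: "Similar analyses will be conducted for the other secondary outcomes". No simpler model is named for the case where the slope cannot be estimated.

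**The concern.** A random slope describes how patients differ in their change over time. To separate that from a patient's general level and from chance variation, a model normally needs more than two occasions. It needs them all the more when each occasion yields only yes or no. With two binary responses, the spread of individual trends is not something the data show.

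This matters because the plan uses that spread in two ways. It tests whether the spread exists, and it asks which risk factors account for it. In a logistic mixed model the fixed time coefficient is also conditional on the random effects, so its size and its z statistic move with the slope SD. If the data cannot choose that SD, the reported time trend reflects an arbitrary value. PTSD is the article's main secondary outcome, and whether AWP alters its course is a stated question.

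**Working it through.** **Inputs from the protocol article.** Two assessments (Outcome measures, Table 1); binary outcome, patient random intercept and random slope (Proposed statistical methods); total sample 3090 (Sample size justification); response of about 40% (Discussion), so 0.40 × 3090 = 1236. No sample size or precision is stated for this model, so there is no plan figure to reproduce. The 1192 under Sample size justification belongs to the 30-day AWP-PTSD model and is not in question.

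**Assumed for illustration only.** Baseline logit -2.2, time effect -0.2, AWP effect 1.5, AWP-by-time 0.3, intercept SD 1.5, slope SD 0.8, zero covariance, AWP prevalence 2% (about the mean of the planned 3.3% and 0.6%), and both responses present for all 1236 patients. The parameter counts in steps 1 and 2 need none of these.

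**Step 1: count, without covariates.** Two binary responses give 2 × 2 = 4 cells, so 4 - 1 = 3 free probabilities. The parameters are intercept, time, intercept variance, slope variance and covariance, which is 5. The 3 × 5 matrix of derivatives has rank 3. Setting the covariance to zero still leaves 4 parameters for 3 probabilities. With a random intercept only there are 3 parameters for 3 probabilities, and the model is identified (condition number of the information matrix about 12).

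**Step 2: add AWP and AWP-by-time.** There are two covariate patterns, so 2 × 3 = 6 free probabilities, against 5 + 2 = 7 parameters. The information matrix is singular.

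**Step 3: same data, different slope SD.** Take the cell probabilities that the assumed values imply for patients without AWP: 0.727 (neither day), 0.105 (day 180 only), 0.111 (day 30 only), 0.056 (both). Refit with the slope SD held at 0, 0.5, 1, 2 and 3. Every fit reproduces the four cells to rounding error, while the time coefficient goes through -0.06, -0.12, -0.27, -0.77 and -1.39. The marginal prevalences are the same in all five fits: 0.111 + 0.056 = 0.167 at day 30 and 0.105 + 0.056 = 0.161 at day 180.

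**Step 4: consequence for the tests (n = 1236, AWP in the model).**

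| Slope SD held at | Log-likelihood | Time estimate (z) | AWP-by-time estimate (SE; z) |
|---|---|---|---|
| 0 | -1091.4867 | -0.06 (-0.47) | 0.19 (0.69; 0.28) |
| 1 | -1091.4866 | -0.27 (-2.04) | 0.36 (0.76; 0.47) |
| 2 | -1091.4870 | -0.77 (-4.78) | 0.74 (0.91; 0.82) |
| 3 | -1091.4874 | -1.39 (-6.89) | 1.22 (1.11; 1.10) |

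The log-likelihood varies by 1091.4874 - 1091.4866 = 0.0008. The data cannot tell the rows apart, yet the time effect passes from nowhere near significant to overwhelming.

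**Step 5: one continuous covariate added.** The information matrix is now formally non-singular, through the curvature of the logit. The standard error of the slope-SD parameter (true value 0.8) is about 8 at n = 1236 and about 5 at n = 3090. The AWP-by-time standard error at 1236 is 0.88, against 0.72 with a random intercept only. If the covariate is also given its own time interaction, the AWP-by-time standard error under the full model rises to about 5.3, against 0.72.

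**Step 6: HADS and EQ-5D, if analysed as continuous.** With time coded 0 and 1, intercept variance A, slope variance B, covariance C and residual variance R: Var(Y1) = A + R; Var(Y2) = A + 2C + B + R; Cov(Y1, Y2) = A + C. That is 3 moments for 4 unknowns (rank 3 of 4), so B and R cannot be separated.

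**The case against.** **Covariates are planned.** The 3-against-5 count is for a model without covariates, and the article plans several. A reader might infer that the model cannot be estimated at any sample size. That goes too far: continuous covariates give formal identification. What they do not give is useful information, as a standard error of about 8 for a true value of 0.8 shows.

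**The AWP question can survive.** A reader might infer that every test of a time trend is empty. The wording "by testing interaction between random time slope and risk factor(s" can be read as an ordinary fixed time-by-factor interaction, and in Step 4 the AWP-by-time z moves only from 0.28 to 1.10, without crossing the 5% level. With a larger assumed interaction, z went from 2.44 to 2.73 as the slope SD went from 0 to 1, and to 3.60 at an SD of 3; again the conclusion held. So this test is less affected, although its estimate shifts and Step 5 shows that its precision depends on what else is in the model.

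**HADS and EQ-5D.** A reader might infer that their tests would be invalid. In a linear mixed model the fixed-effect tests depend only on the marginal 2 × 2 covariance, which is identified, so they stand. The article also says only that similar analyses will be done, so the exact model is an inference.

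**Convergence and response.** A reader might expect certain software failure, or blame the 40% response. Nothing in the article shows either. It does not say how responses divide between the two days.

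**The slope may be tested and dropped.** The article does say the random effects will be tested. But that test is the empty part: a flat likelihood gives no basis for keeping or removing the slope.

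**Conclusion.** The point holds in a limited form. As written, the random-slope variance and the intercept-slope covariance are not identified from two binary responses, or are identified only through the link function with almost no information. Three planned outputs therefore depend on an arbitrary slope SD: the test of the random slope, any statement that risk factors explain slope variation, and the subject-specific time effect. In the illustration that dependence is large for the time effect (z from -0.47 to -6.89 at an indistinguishable likelihood) and smaller for AWP-by-time (estimate 0.19 to 1.22, z 0.28 to 1.10). For continuous HADS and EQ-5D, only the split between slope and residual variance fails.

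The parameter counts rest on the article alone; the z values and standard errors rest on the assumed effect sizes, 2% AWP prevalence and complete pairs. The primary AWP analysis, the control-versus-intervention PTSD comparison, the 30-day AWP-PTSD model and the mediation analysis are not touched. The change should be made, but it concerns one secondary analysis.

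**What to change.** Remove the random time slope and the test of its variance. Specify a logistic model for PCL-5 above 32 with a patient random intercept, a fixed indicator for day 180 versus day 30, and fixed interactions of that indicator with AWP and with each listed risk factor. Keep site as a fixed effect. The interactions answer the article's question about what alters the time trend. GEE with patient as the cluster is an alternative if a marginal effect is wanted; the text should say which effect is the target, because the two differ in meaning.

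Apply the same structure to HADS and EQ-5D: a patient random intercept, the day indicator and its fixed interactions.

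Under the assumptions above, the random-intercept model at n = 1236 gives a standard error of about 0.13 for time and 0.70 for AWP-by-time. The model is therefore estimable, but the article should not promise much precision on the AWP interaction. The cost is a change of analysis wording, with no new data, visits or patients.

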## Methods

### Trial design

This is a multicenter, pragmatic, stepped wedge cluster randomized superiority trial enrolling at five academic sites over an approximately 3.5-year period, divided into six time periods of 6 months each. A schematic of the trial design appears in Fig. 3. Prior to the trial, each site (one site equals one cluster) was randomly allocated to their position within the design. One cluster will cross to the intervention period, at which point succinylcholine will become the default NMB in the ED, every 6 months (i.e., step duration) from the 2nd to the 6th time period. Cluster order will be determined by computer-based randomization, conducted and generated by the trial statistician (YY), and concealed from each site. To begin, each site will be exposed to control conditions; by the end of the trial, each site will be exposed to the intervention. Enrollment began in June of 2023 and we anticipate recruitment of the total sample size to be completed by September of 2026.

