### Proposed statistical methods

Patient characteristics will be reported using descriptive statistics and frequency distributions. Continuous variables will be compared using independent samples *t*-test or Mann–Whitney *U* test, and categorical variables will be compared using chi-square test or Fisher’s exact test.

AWP will be calculated as proportion (with 95% confidence intervals [CI]) of patients with possible or definite events, as done before [19, 20, 57]. Adjudicator agreement will be assessed, per prior approach, with two-way, random effects, intraclass correlation coefficient for absolute agreement according to 0 = no awareness, 1 = possible awareness, and 2 = definite awareness. All analyses will be intention to treat, such that all patients will be evaluated, regardless of clinician adherence during the intervention phase. The unit of randomization will be the ED, and the unit of analysis will be the patient. The primary analysis will compare the proportion of patients with AWP in the control phase versus the intervention phase. To estimate the intervention effect, mixed effects models and generalized estimating equations (GEE) are most commonly used in stepped wedge designs. However, due to the smaller number of clusters (*n* = 5), it is more appropriate to use a generalized linear model, with cluster included as a fixed effect (i.e., a logistic regression model for binary outcome data with each of five sites as fixed effect) [75–78]. We will first fit a basic model, in which the intervention effect is estimated, adjusting for secular trends (i.e., time effect). We will then extend the basic model by incorporating and testing appropriate interaction terms to test the nature of the intervention effect. Examples include (1) an intervention-by-cluster interaction for heterogeneity of the intervention effect across clusters; and (2) an intervention-by-time for heterogeneity of the intervention effect across time. A possible delayed intervention effect will be tested by changing the intervention indicator (i.e., 0 or 1) into some fractions between 0 and 1, aligned with the time from switching from control to intervention. Unadjusted analyses will also be reported.

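### The control-versus-intervention comparisons of PTSD symptoms and the other secondary outcomes are stated without the calendar-time adjustment that the AWP model has, so any secular trend would be read as an intervention effect

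*Protocol article*

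**What the plan says.** All of this is in the Protocol article, Proposed statistical methods, unless noted.

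- **AWP.** A logistic model has the five sites as fixed effects, and "We will first fit a basic model, in which the intervention effect is estimated, adjusting for secular trends (i.e., time effect". A later sentence adds: "Unadjusted analyses will also be reported".
- **Instrumental-variable (CACE) analyses.** Step-specific estimates are used so that time is not mistaken for the intervention, and the two-stage regression adjusts for time and cluster.
- **PTSD symptoms, days 30 and 180.** Proportions with confidence intervals will be determined, and the plan will "compare the control versus the intervention phase". That sentence names no model and no adjustment.
- **Further PTSD models.** A logistic model relates AWP to day-30 symptoms with patient covariates, and a mixed logistic model has individual random intercepts and time slopes. Then: "In all of these models, cluster effect will be modeled as a fixed effect, using cluster indicator in the model".
- **Other secondary outcomes.** They are to be handled in the same way as PTSD.
- **Layout (Trial design).** "One cluster will cross to the intervention period, at which point succinylcholine will become the default NMB in the ED, every 6 months", from the second to the sixth of six periods.

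**The concern.** In a stepped wedge, phase and calendar time are tied together by design. A phase comparison without a period term tests a joint null of no intervention effect and no calendar trend. Putting site in the model does not help with this, because the confounding with time lies within each site.

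PTSD is the main secondary outcome. Over about three years, drift in case mix, in ICU care, or in which survivors answer the telephone could shift the PTSD proportion with no contribution from the neuromuscular blocker policy. The same holds for HADS and EQ-5D. The article recognises this hazard for AWP and CACE but does not carry the protection over to these outcomes.

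**Working it through.** **1. The plan's own figure.** "Considering there are 5 sites and 6 time periods, for 80% power" leads to "we will need a total sample size 3090 patients". The formula is not given. The Hussey–Hughes variance, which includes period effects, reproduces it, taking a two-sided 0.05 test (sidedness is not stated for AWP), ICC 0.001 and rates of 3.3% and 0.6%:

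- Per cell 3,090/30 = 103; σ² = 0.033 × 0.967 = 0.03191; s = σ²/103 = 0.0003098; τ² = (0.001/0.999)σ² = 0.00003194.
- With I = 5 sites, T = 6 periods, U = 15, W = 55 and V = 55: IU − W = 20 and U² + ITU − TW − IV = 70.
- Variance = 5s(s + 6τ²)/(20s + 70τ²) = 0.00009212, so SE = 0.00960.
- Power = Φ(0.027/0.00960 − 1.96) = 80.3%. At 3,060 patients it is 79.98%.

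The stated size is therefore consistent with period adjustment being part of the design.

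**2. How far apart the phases lie in time.**

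- Mean period, control cells: (1×5 + 2×4 + 3×3 + 4×2 + 5×1)/15 = 2.33.
- Mean period, intervention cells: (2×1 + 3×2 + 4×3 + 5×4 + 6×5)/15 = 4.67. The crude gap is 2.33 periods, or 14 months.
- Within a site with k control periods: control mean (k + 1)/2, intervention mean (k + 7)/2, gap 3 periods, or 18 months, for every k.

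A site-only model thus picks up slightly more of a trend than a crude comparison. With trend odds ratio t per period, its spurious phase odds ratio is about t³: 0.95³ = 0.86 and 0.90³ = 0.73.

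**3. Precision of the PTSD phase effect.** Inputs are 40% response (Discussion), which gives 1,236 patients or about 41 per cell, and a 20% PTSD rate (Sample size justification, patients without AWP).

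- Site only: information = 41 × 0.20 × 0.80 × (5 + 8 + 9 + 8 + 5)/6 = 38.3, so SE = 0.162.
- Site and period: the residual sum of squares of the phase indicator is 15 − 55/6 − 55/5 + 225/30 = 2.33. Information = 41 × 0.16 × 2.33 = 15.3, so SE = 0.256 (0.257 by simulation).
- Variance ratio = 5.83/2.33 = 2.5.
- Odds ratio detectable with 80% power: exp(2.80 × 0.162) = 1.57 against exp(2.80 × 0.257) = 2.05.

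**4. False-positive rate with no intervention effect, nominal 5%.** Trend sizes and site PTSD rates of 20–35% are assumptions. Simulation used 41 per cell and logistic Wald tests; ranges cover repeated runs. The approximation is Φ(z − 1.96) + Φ(−z − 1.96), with z = 3|ln t|/SE and SE = 0.145 at the mid-range rate of 27.5%.

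| Trend OR per period | First to last period (t⁵) | Site only, approximation | Site only, simulated | Site + period, simulated |
|---|---|---|---|---|
| 1 | 1 | 5% | about 5% | 4–6% |
| 0.97 | 0.86 | 10% | about 9% | 4–6% |
| 0.95 / 1.05 | 0.77 / 1.28 | 19% / 17% | 15–19% | 4–6% |
| 0.90 / 1.10 | 0.59 / 1.61 | 59% / 51% | about 50–57% | 4–6% |

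At a flat 20% rate, a first-to-last odds ratio of 1.5 (17.0% rising to 23.4%) gives 26% rejection for the crude test, 33% for site only and 4% for site plus period.

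**The case against.** The strongest reply is that this is silence in a condensed article. The AWP model is introduced as the way to estimate the intervention effect, the article commits to the CONSORT stepped-wedge extension, and a full analysis plan may apply the same model throughout. The site-indicator sentence closes a paragraph on models whose exposure is AWP, not phase. This stands in part: a reader might infer that the authors have decided on a site-only phase test for PTSD, and the text does not say that. It does state the comparison and does name time adjustment elsewhere, so an analysis that follows the wording would leave period out.

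The sizes are also open to challenge. The documents give no PTSD trend, and 0.90 or 1.10 per period is a large drift. The one documented trend is rocuronium uptake, which bears on AWP. That slope and the stated odds ratio of 6.05 imply an AWP odds ratio of about 1.18 over three years; at 1.2, a crude AWP test rejects in about 7% of trials. This stands, and it is why the result is given as a range that starts at 5%.

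Three wider readings do not hold:

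- The sentence that "categorical variables will be compared using chi-square test or Fisher’s exact test" sits in the paragraph on patient characteristics. It does not prescribe a crude test of outcomes by phase.
- The unadjusted AWP result is labelled as such and supplements an adjusted primary model. No decision rests on it.
- Differences between sites distort only crude comparisons. Once site is in the model, calendar trend is the remaining problem.

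**Conclusion.** The point holds for the control-versus-intervention comparisons of PTSD symptoms at days 30 and 180 and of the other secondary outcomes handled like them. As written, these comparisons lack the calendar-time term that the design requires and that the plan gives AWP and CACE. The structural part needs only the layout in Trial design: the three-period gap within each site is exact for equal periods. The false-positive rates also rest on assumed trends, assumed site rates, equal cell sizes and 40% response. With no trend a site-only test keeps its 5%.

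A reader might infer that the trial's main conclusion is at risk. It is not, because the primary AWP model carries both site and time. The matter should be settled before the secondary outcomes are analysed.

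**What to change.** State in Proposed statistical methods that the control-versus-intervention comparisons of PTSD symptoms (days 30 and 180), HADS and EQ-5D use the AWP model's design terms: site fixed effects, calendar-period fixed effects and the intervention term, with a link suited to each outcome. Say that follow-up time in the PTSD mixed model is distinct from calendar period. Present crude proportions by phase as descriptive.

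No change is asked to the patient-characteristics tests or to the labelled unadjusted AWP analysis. Nor is a site-and-period model asked for very rare safety events such as malignant hyperthermia: at 0.009% of 3,090 patients, about 0.3 events are expected, too few to fit one.

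The change is wording only and needs no new data. The cost is precision: about 2.5 times the variance of the PTSD phase effect, which moves the detectable odds ratio from about 1.57 to about 2.05 at 40% response. The plan should acknowledge that the phase comparison for PTSD will then be informative only for large effects.
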